## Abstract

**Introduction:**

Care for head and neck cancers is complex in particular for the rare ones. Knowledge is limited and histological heterogeneity adds complexity to the rarity. There is a wide consensus that to support clinical research on rare cancer, clinical registries should be developed within networks specializing in rare cancers. In the EU, a unique opportunity is provided by the European Reference Networks (ERN). The ERN EURACAN is dedicated to rare adults solid cancers, here we present the protocol of the EURACAN registry on rare head and neck cancers (ClinicalTrials.gov Identifier: NCT05483374).

**Study design:**

Registry-based cohort study including only people with rare head and neck cancers.

**Objectives:**

**Methods:**

Settings and participants

It is an hospital based registry established in hospitals with expertise in head and neck cancers. Only adult patients with epithelial tumours of nasopharynx; nasal cavity and paranasal sinuses; salivary gland cancer in large and small salivary glands; and middle ear will be included in the registry. This registry won’t select a sample of patients. Each patient in the facility who meets the above mentioned inclusion criteria will be followed prospectively and longitudinally with follow-up at cancer progression and / or cancer relapse or patient death. It is a secondary use of data which will be collected from the clinical records. The data collected for the registry will not entail further examinations or admissions to the facility and/or additional appointments to those normally provided for the patient follow-up.

Variables

Data will be collected on patient characteristics (eg. patient demographics, lifestyle, medical history, health status); exposure data (eg. disease, procedures, treatments of interest) and outcomes (e.g. survival, progression, progression-free survival, etc.). In addition, data on potential confounders (e.g. comorbidity; functional status etc.) will be also collected.

Statistical methods

The data analyses will include descriptive statistics showing patterns of patients’ and cancers’ variables and indicators describing the quality of care. Multivariable Cox’s proportional hazards model and Hazard ratios (HR) for all-cause or cause specific mortality will be used to determine independent predictors of overall survival, recurrence etc. Variables to include in the multivariable regression model will be selected based on the results of univariable analysis. The role of confounding or effect modifiers will be evaluated using stratified analysis or sensitivity analysis. To assess treatment effectiveness, multivariable models with propensity score adjustment and progression-free survival will be performed. Adequate statistical (eg. marginal structural model) methods will be used if time-varying treatments/confounders and confounding by indication (selective prescribing) will be present.

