### Data analyses plan

The data analyses will include descriptive statistics showing frequency and patterns of patients’ and cancers’ variables; analytical analyses investigating the association of patients/disease and/or treatment characteristics and health outcomes.

Descriptive statistics will be used to reconstruct the natural history of rare head and neck cancers (e.g. primary tumour growth rate and pattern, its metastatic dissemination, growth of metastases, association with other diseases etc.) and to report indicators about quality of care.

Multivariable Cox’s proportional hazards model and Hazard ratios (HR) for all-cause or cause specific mortality will be used to determine independent predictors of overall survival, recurrence and second primary cancer. Variables to include in the multivariable regression model will be selected based on the results of univariable analysis or using Information Criteria, such as Akaike Information Criterion. According to the specific research question the role of potential confounders and effect modifiers will be evaluated. Confounders will be included in the model and sensitivity analysis will be performed. Stratified analyses will be performed in the presence of effect modifiers that will be detected by testing the interaction between the predictors and the variable.

To assess treatment effectiveness multivariable models with propensity score adjustment that can remove bias due to real world nature of the registry and progression-free survival will be performed.

High proportion of missing data threaten the validity of the inferences/prognostic models. Thus, a maximum of 10% of missing data will be allowed and missing data will be imputed using strategy such as unconditional/conditional mean or expectation maximum.

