### Outcomes

Primary outcomes with a time frame of 1 year include:

Overall survival (all cause and/or cause specific)Disease free survivalTreatment response: the percentage of patients whose cancer shrinks or disappears after treatment. Treatment response expressed as a complete response; partial response; stable disease; progression based on clinical judgment on imaging.Cancer treatment observed adverse events: incidence of cancer treatment adverse events as assessed by Common Terminology Criteria for Adverse Events (CTCAE)Surgical complications: percentage of patients with surgical complications as assessed by the Clavien-Dindo ClassificationQuality of care: percentage of patients treated according to clinical practice guidelines for head and neck cancer.

Predictors of mortality and/or tumor response include but are not limited to:

Patients’ Characteristics (age, gender, educational level, tobacco, comorbidity, virus status when appropriate)Tumor Characteristics (site, histology, T,N,M, clinical and pathological stage, tumour mutation)Treatment Characteristics (radiotherapy alone, surgery alone, systemic therapy alone, multimodal therapy)

Exposures will mainly include different type of treatment (radiotherapy alone, surgery alone, systemic therapy alone, multimodal therapy)

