**Fig 1 pone.0283071.g001:**
[figure not shown]
Data quality checks implemented in R.

After the corrections made by the data providers, all checks will be re-run and quality reports reviewed by INT. Interaction with data providers will be reiterated until sufficient data quality is achieved. The DB with sufficient data quality will be saved and used for the federated learning analysis. These checks will be performed annually and will ensure high data quality within a federated DB. The degree of data completeness will be summarized and available for the researchers and consumers of the analysis of the registry.

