## Discussion

Limitations

There is a risk of limited representativeness due to the hospital-based nature of the registry and to the fact that hospital contributing to the registry are expert centres for these rare cancers. Representativeness of the registry will be tested comparing the registry data with population-based data in terms of relevant variables (eg. age, stage, prognosis). Adequate statistical (eg. marginal structural model) methods will be used if time-varying treatments/confounders and confounding by indication (selective prescribing) will be present, not to raise methodological problems.

Directed acyclic graphs can also be useful to identify the source of bias and will be utilized in the definitions of the path between covariates. Close collaboration with clinicians will be crucial also in this part to allow a proper interpretation of the registry data [7]. Clinical Follow-up could be an issue but active search of the life status of the patients will be guaranteed.

Dissemination plan

In order to ensure the appropriate access, use and dissemination of the data, the registry will be supervised by a Steering Committee (SC) with the following tasks:

to launch, plan, supervise and approve studies and publications based on the registry datato ensure adherence to the publication policy and to the guidelines for accessing the registry datato plan and endorse modifications of the registry structure (e.g., pathologic classification or staging changes etc.)deliberate on requests of enrollment into the EURACAN Registry from non EURACAN centres or networks linked to itto discuss and agree amendments to the registryonce the registry is fully functioning, to promote the use of the registry data also for international collaborative studies (e.g. with US, Rare Cancers Asia, etc.), in other words ensure that the EURACAN Registry will be **FAIR** (findable, accessible, interoperable, reusable)to review the EURACAN registry governanceto identify opportunities for financial support to maintain the registry.

Data access rules

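### Follow-up is described as triggered by outcome events, and only life status is guaranteed for other patients, so relapse- and progression-based estimates are at risk of bias

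*Protocol article*

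**What the plan says.** The statement of when patients are followed is in the abstract (Methods, Settings and participants): each eligible patient "will be followed prospectively and longitudinally with follow-up at cancer progression and / or cancer relapse or patient death". The same paragraph says the data come from clinical records, with no "additional appointments to those normally provided for the patient follow-up".

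The abstract's Results and the Discussion (Limitations) both acknowledge a weakness and give one safeguard: "Clinical Follow-up could be an issue but active search of the life status of the patients will be guaranteed".

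The one recurring activity described, under Data quality checks, covers validity, plausibility and completeness of entered data: "These checks will be performed annually and will ensure high data quality within a federated DB". It is not described as a refresh of disease status.

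Several analyses need to know when an event-free patient was last seen free of disease:
- Disease-free survival is among the primary outcomes, listed under "Primary outcomes with a time frame of 1 year include".
- Progression-free survival serves the treatment-effectiveness aim (Data analyses plan).
- Cox models "will be used to determine independent predictors of overall survival, recurrence and second primary cancer" (same section).

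**The concern.** Each named follow-up trigger is itself an outcome. A site that works to that sentence reopens the record of a patient who relapses, progresses or dies, and has no stated reason to reopen the record of a patient who stays well. The life-status search then tells the registry that this patient is alive, but not whether the disease has returned.

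The length of recorded disease follow-up could therefore depend on having had the event, which is informative censoring. An out-of-date record can also pass the annual checks, because nothing in it is invalid, implausible or blank.

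A later analysis plan can choose a censoring date only from the dates that were collected. With data held separately by each hospital or registry, rebuilding the dates years later would be harder than recording them as they arise.

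**Working it through.** The article gives no figure on this point, so there is none to reproduce. The calculations show size and direction only, and none of their inputs comes from the article.

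**1. Event-free patients censored at an old form (downward bias)**

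Assumptions: constant hazard, true 2-year PFS 70%, administrative follow-up uniform over 0 to 6 years, and a fraction p of event-free patients with no update after month 6.

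- Hazard: λ = −ln(0.70)/2 = 0.178 per year.
- True 1-year PFS: 0.70^0.5 = 84%. True 5-year PFS: 0.70^2.5 = 41%.
- Let S(t) = exp(−λt). Let E(t) = ∫ₜ⁶ λS(u)(1 − u/6) du be the share whose event is still to be recorded, and F(t) = ∫ₜ⁶ S(c)/6 dc the share who will end event-free. Then E(t) + F(t) = S(t)(1 − t/6), the correct risk set.
- After month 6 the risk set loses pF(t) while the events are unchanged, so the apparent hazard is λ(E + F)/(E + (1 − p)F).
- Just after month 6, E = 0.304 and F = 0.534. For p = 0.50 the apparent hazard is 0.178 × 0.838/(0.304 + 0.267) = 0.262, about 1.47 times the true value.

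Integrating this hazard agrees with simulation:

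| Not updated after month 6 | 1-year PFS (true 84%) | 2-year PFS (true 70%) | 5-year PFS (true 41%) |
|---|---|---|---|
| 25% | 82% | 66% | 34% |
| 50% | 80% | 61% | 25% |
| 75% | 77% | 53% | 13% |

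**2. The same fractions, but records only 12 months out of date**

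The 2-year estimate is about 69%, 67–68% and 66% against 70%. How stale the date is matters as much as how many records are stale.

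**3. Event-free patients carried to the life-status date (upward bias)**

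Assumptions: true 3-year PFS of 50%, 65% or 80%; 80% of first events are relapses; mean survival after relapse 1.5 years; administrative follow-up of 1 to 8 years; vital status always known; clinical contact lost at 0 to 20% per year.

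- No loss of contact: no bias.
- Loss of 5 to 20% per year: 3-year PFS reads 0.515–0.546, 0.660–0.684 and 0.806–0.821 against 0.50, 0.65 and 0.80.
- At 1 year the largest excess is about 0.012 (0.806 against 0.794).

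**4. Censoring at a refreshed last disease assessment**

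In the setting of step 3, the 3-year values are recovered to within 0.003 and the 1-year values to within 0.001 at every loss rate tried, provided that loss of contact is unrelated to prognosis.

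**5. Comparisons between groups**

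With identical true hazards and the month-6 freeze of step 1, equal stale fractions give a hazard ratio of 1.0. Unequal fractions do not: 10% against 50% gives about 1.3 to 1.4, and 25% against 75% about 1.6. A propensity score built on baseline covariates would not remove this.

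**The case against.** The strongest case on the other side is that the article does not restrict data entry to events. It does not use the word only. The sentence can be read as naming the outcomes to be captured, and the same paragraph relies on routine follow-up visits and clinical records. The inclusion criteria ask sites to cover the whole disease course, and patients diagnosed before 2021 must be in active hospital follow-up. Treatment response and adverse events, which are not among the triggers, are primary outcomes. Variable-level detail sits in a code book that is not shown and may well hold a last-assessment date. Censoring rules normally belong in an analysis plan.

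Most of this stands, and it rules out three stronger readings:
- **Event-free patients have no current disease-status date.** This cannot be shown without the code book, and routine records could supply a date.
- **The estimates are biased.** Direction and size depend on the censoring date and on loss of clinical contact. The bias can be nil, and it is smaller at the stated 1-year time frame than later.
- **Centre or treatment differences will be artefacts.** That needs updating to differ between the groups compared, which the documents do not quantify.

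A reader might also infer that the natural-history aim fails for want of serial status ("primary tumour growth rate and pattern, its metastatic dissemination, growth of metastases"). Those items are examples within a descriptive aim, and the inference again assumes that entries are made at events alone.

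What the objection does not remove is that the article states event triggers, admits that clinical follow-up may be a problem, and answers with life status alone. Leaving the censoring rule to a later plan is reasonable. Leaving the date itself uncollected could not be repaired there.

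**Conclusion.** The point holds as a risk. As described, disease follow-up is triggered by events, only life status is guaranteed for everyone else, and no periodic disease-status update is stated. Disease-free survival, progression-free survival and recurrence are exposed; overall survival is largely protected.

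On the assumptions in steps 1 and 2 of the working, the 1-year estimate falls by about 2 to 7 percentage points and the 2-year estimate by about 4 to 17 if records freeze at month 6. The 2-year loss is only about 1 to 4 points if records are 12 months stale. In the opposite direction, the 1-year excess is at most about 1 point. The freeze date, the stale fractions and the loss rates are all assumed.

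Confidence is moderate because the code book has not been seen. This is a worthwhile and inexpensive improvement, and not a defect that must be cured before the registry can proceed.

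**What to change.** Keep the event-triggered entries. At the existing annual data-quality cycle, add three items for every living patient, taken from routine records:
- date of last disease assessment;
- disease status at that date;
- date last known alive.

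State that disease-free and progression-free survival are censored at the last disease assessment, and overall survival at the date last known alive. In the annual summary report, flag records not updated in the past 12 months, so that uneven updating between sites becomes visible.

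If the code book already requires these dates, it is enough to correct the follow-up sentence in the abstract to say so.

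The cost is modest data-entry time at sites: three fields per patient per year. No extra visits or examinations are needed, so the registry's secondary-use principle is kept. The remaining limit is that censoring at the last assessment removes the bias only if loss of clinical contact is unrelated to prognosis.

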**Results:**

The registry initiated recruiting in May 2022. The estimated completion date is December 2030 upon agreement on the achievement of all the registry objectives. As of October 2022, the registry is recruiting. There will be a risk of limited representativeness due to the hospital-based nature of the registry and to the fact that hospital contributing to the registry are expert centres for these rare cancers. Clinical Follow-up could also be an issue but active search of the life status of the patients will be guaranteed.

## Introduction

Despite the rarity of each of the 198 identified rare cancers (RC), collectively they represent 24% of all new cancer cases diagnosed in the EU28/yearly [1]. Differences in survival for RC exist across European countries suggesting the existence of inequalities in healthcare [2]. Rare cancers in general get less scientific consideration and financial support than their more common counterparts. The generation of clinical evidence is more difficult due to the difficulties of conducting clinical trials for to the small number of patients and the paucity of accessible data, including data from cancer registries.

Europe is covered by widespread population-based cancer registries (CRs). However, clinically relevant data, e.g. on detection, staging, treatment and treatment effects tend to lack across CRs [3]. Ad hoc observational studies (i.e. high-resolution study) [4] are costly and time consuming, too often lack detailed information and are not able to provide it in real-time. In its Rare Cancer Agenda 2030 (https://www.rarecancerseurope.org/rce-jarc/rare-cancer-agenda-2030) the JARC recommended developing clinical registries on RC within networks specializing in RCs to support clinical research.

In the EU, a unique opportunity is provided by the European Reference Networks (ERNs). The ERNs are virtual networks of selected institutions targeting rare conditions. Three ERNs are dedicated to rare cancers: EuroBloodNet for rare haematological diseases, PaedCan for paediatric cancers and EURACAN for rare adult solid cancers (RAC). EURACAN is focusing on 10 out of the 12 families of rare cancers (corresponding to 75% of all rare cancers), each corresponding to a EURACAN “domain”: G1, sarcomas; G2, rare neoplasms of the female genital organs and placenta; G3, rare genitourinary cancers; G4, neuroendocrine tumours; G5, rare gastrointestinal cancers; G6, endocrine cancers; G7, rare head and neck cancers; G8, rare thoracic cancers; G9, rare skin/eye melanoma; G10, central nervous system tumours.

An EU-supported project Starting an Adult Rare Tumour Registry (STARTER) began on April 1^st^ 2020 to develop the EURACAN registry.

The registry initiated on the rare head and neck cancers including nasal cavity and paranasal sinuses (incidence rate 0.5/100,000), nasopharynx (incidence rate 0.5/100,000), salivary gland (incidence rate 1.5/100,000) and middle ear cancers (incidence rate 0.03/100,000), corresponding to 2,500, 2,500, about 8,000 and about 200 new cases/year in Europe, respectively (http://rarecarenet.istitutotumori.mi.it/analysis.php). Cancer care for head and neck cancers is complex in particular for the rare ones. Knowledge is limited, diseases often need multidisciplinary approach, including surgery, radiation, and systemic treatments. Patients tend to be older, to have comorbidities and less social support [5]. Moreover, while most head and neck cancers are predominantly squamous cell carcinomas, salivary gland tumours include more than 20 distinct histological subtypes. A similar consideration holds for paranasal sinus cancers. Thus, heterogeneity adds complexity to the rarity.

Our hypothesis is that the registry, gathering data on rare head and neck cancers, will support research to increase their understanding. The new evidence will contribute to develop and/or ameliorate clinical practice guidelines, to support multidisciplinary discussion and consultations for patients with rare head and neck cancers and ultimately to improve quality of care across Europe.

## Materials and methods

Registry aims

to help describe the natural history of rare head and neck cancers;to evaluate factors that influence prognosis;to assess treatment effectiveness;to measure indicators of quality of care.

Furthermore, the registry aims to collect information, where available, on the storage of biological samples at the premises of the participating healthcare providers (HCPs). This will facilitate future studies on rare head and neck cancers biology.

Design and setting

The registry is designed to prospectively collect clinical data derived from diagnostic tests and treatments performed by the HCP as part of patient management. The data collected for the registry will not entail further examinations or admissions to the HCP and/or additional appointments to those normally provided. In other words, it will be an observational, registry-based cohort study including only people with rare head and neck cancers.

The EURACAN Registry will include EURACAN HCPs (across 7 different EU member States) and will be open to other expert HCPs, not yet in EURACAN but with proven experience in rare head and neck cancers.

### Inclusion criteria

Patients with epithelial tumours of nasopharynx; nasal cavity and paranasal sinuses; salivary gland cancer in large and small salivary glands; and middle ear (i.e. squamous carcinoma; adenocarcinoma; neuroendocrine; adenosquamous carcinoma, teratocarcinosarcoma, NUT carcinoma, odontogenic tumours) + neuroendocrine and adenocarcinoma in hypopharynx; oropharynx; larynx; oral cavity and lip + odontogenic carcinoma in oral cavity.Adult patients (aged ≥18 years).Diagnosis performed or verified by the expert centre entering the patient information in the registry.Patients entering the HCP at any clinical phase of the disease (diagnosis, treatment of primary cancer, treatment of recurrence, treatment of M+ etc.). The HCP will collect information on the entire course of the disease regardless of when it started to manage the patient. The HCP can decide, based on its resources, the number of patients on whom it can collect data.New patients managed by the HCP from 2021 onwards plus patients managed by the HCP, who are actively followed up at the hospital, with year of diagnosis dating back to maximum 2018.

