### Sample size

This is an observational clinical registry which implies a long-term data collection lasting until all the registry objectives are met. Only HCPs that treat at least 100 cases a year of all rare head and neck cancers are EURACAN member. As of April 2022, the registry is activating 10 HCPs and, with time, is envisioning to at least duplicate the number of data providers. Considering that we expected 6 centres in Italy, 2 centres in Germany, 1 centre in Czech Republic, 1 centre in Spain, 2 centres in France (400 cases per year)and the whole rare head and neck cases in The Netherlands (300 patients yearly, based on incidence estimations), we expect about 1700 patients with a rare head and neck cancer yearly.

Due to the observational nature of the registry, sample size justification is based on the precision of the estimates presented in terms of width of two-sided 95% Confidence Interval (CI) for a single proportion using the Simple Asymptotic method (in case of categorical variables) and in form of normal distribution for means (in case of continuous variables). Thus, for example, for a categorical endpoint (e.g., proportion) a sample size of 80 patients (e.g. middle ear cases in 4 years) will achieve a maximum width of 95% CI on estimated proportions of 23.4% (i.e. estimated proportion +/- 11.7%). For continuous endpoints, a sample size of 80 patients will achieve a maximum width of 95% CI on estimated means of 0.46*SD (i.e. estimated mean +/- 0.23*SD, where SD = Standard Deviation).

Table 1 reports the precision of the estimates for categorical and continuous endpoint under different sample size.

**Table 1 pone.0283071.t001:** Precision of the estimates expressed as 95% Confidence Interval (CI) for categorical and continuous endpoint accordingly to different sample size.

		
	Categorical endpoint		Continuous endpoint	
Target sample size	max 95% CI	Width of 95% CI (%)	max 95% CI	Width of 95% CI
1000	Estimate +/-0.03	0.06	Estimate +/- 0.06*SD	0.12*SD
250	Estimate +/- 0.06	0.12	Estimate +/- 0.12*SD	0.24*SD
80	Estimate +/- 0.11	0.22	Estimate +/- 0.22*SD	0.44*SD
70	Estimate +/- 0.12	0.24	Estimate +/- 0.23*SD	0.46*SD
60	Estimate +/- 0.13	0.26	Estimate +/- 0.25*SD	0.50*SD
50	Estimate +/- 0.14	0.28	Estimate +/- 0.27*SD	0.55*SD

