### Status and timeline of the registry

The registry initiated recruiting in May 2022. The estimated completion date is December 2030 upon agreement on the achievement of all the registry objectives. As of August 2022, the registry is recruiting.

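### The abstract says no sample of patients is selected, but the inclusion criteria let each centre decide how many patients to enter, with no rule for which ones

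*Protocol article*

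**What the plan says.** Two parts of the protocol article describe who enters the registry.

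- **Abstract, Methods (settings and participants):** "This registry won’t select a sample of patients", and "Each patient in the facility who meets the above mentioned inclusion criteria will be followed prospectively and longitudinally".
- **Inclusion criteria:** "The HCP can decide, based on its resources, the number of patients on whom it can collect data". No order or method of choosing patients follows.

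Four other places bear on the point.

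- **Inclusion criteria, time window:** new patients managed from 2021 onwards are eligible. So are earlier patients "who are actively followed up at the hospital, with year of diagnosis dating back to maximum 2018".
- **Status and timeline:** "The registry initiated recruiting in May 2022".
- **Sample size:** "we expect about 1700 patients with a rare head and neck cancer yearly". The section also states the membership threshold: "Only HCPs that treat at least 100 cases a year of all rare head and neck cancers are EURACAN member".
- **Limitations:** limited representativeness is put down to the registry being hospital-based and to its hospitals being expert centres. A comparison with population-based data on variables such as age, stage and prognosis is planned. Selection within a centre is not mentioned.

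**The concern.** A centre that enters only part of its eligible patients is taking a sample, so both statements cannot govern. A reader of the abstract would take the cohort within each hospital to be complete, when the operative criteria allow it not to be.

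This matters because of what the registry reports. The Outcomes section lists survival, treatment response, adverse events, surgical complications and treatment according to guidelines, all with a 1-year time frame. Several of these are absolute percentages, which depend directly on who is entered. The data come from clinical records. Where the first year has already passed when a patient is chosen, the person choosing can see both the outcome and how complete the record is. If either influences the choice, the percentages shift. The article provides no count of eligible patients against which a shift could be detected.

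**Working it through.** **1. The plan's own figure.** The Sample size section counts 6 + 2 + 1 + 1 = 10 centres in Italy, Germany, the Czech Republic and Spain, two French centres with 400 cases a year, and all Dutch cases at 300 a year. Using the membership minimum of 100 for each of the ten centres (an inference, since the article does not show the sum):

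10 × 100 + 400 + 300 = 1700.

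This reproduces the stated figure. It assumes that the counted caseloads are entered in full, which fits the abstract and not the inclusion criteria.

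**2. What a limit would do to that figure.** Let f be the share of the counted caseload that is entered outside the Netherlands (assumed). The yearly total is 1400 × f + 300.

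| f | Yearly total |
|---|---|
| 1.00 | 1700 |
| 0.75 | 1350 |
| 0.50 | 1000 |
| 0.25 | 650 |

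Here f is relative to the counted caseload. A centre that treats more than 100 cases could limit its entry and still supply 100.

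**3. When the outcome can be known.** Take the year from first management at the centre (an assumption). For a patient first managed in early 2021, the full year had passed when recruitment opened in May 2022. For one first managed in later 2021 or early 2022, part of it had passed at opening, and all of it has passed if the record is entered a year or more after first management. For a patient who enters at presentation after May 2022, it is not known.

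**4. Illustration of the bias.** Let S be true 1-year survival, a the probability of entry for patients alive at 1 year, and d that for patients who died. Then

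observed survival = S·a / (S·a + (1 − S)·d).

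For S = 0.80, a = 0.60, d = 0.40: 0.48 / (0.48 + 0.08) = 0.857. With d = 0.30: 0.48 / (0.48 + 0.06) = 0.889.

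| True S | a = d | a = 0.60, d = 0.40 | a = 0.60, d = 0.30 |
|---|---|---|---|
| 0.70 | 0.700 | 0.778 | 0.824 |
| 0.80 | 0.800 | 0.857 | 0.889 |
| 0.90 | 0.900 | 0.931 | 0.947 |

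All values of S, a and d are assumed. Under them the overstatement is about 3 to 12 percentage points in the patients chosen this way, and less in the registry as a whole. The direction can reverse: with S = 0.80, a = 0.40 and d = 0.60, the result is 0.32 / (0.32 + 0.12) = 0.727. Equal entry rates give no bias, so a limit alone does no harm to the estimate.

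**5. Whether another provision covers it.** The data quality checks run on cases already completed in the database. The reports described cover valid core data, treatment by stage, missing values and errors per patient; none counts eligible patients who were not entered. Propensity scores and marginal structural models address treatment confounding among entered patients, not entry itself.

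**The case against.** The criterion gives discretion over the number of patients and ties it to resources. It does not say that centres choose by outcome. Data collection is described as prospective and written consent is required from all participants, so outcome-aware choice is plausible mainly for patients from 2021 to early 2022. The planned comparison with population-based data includes prognosis and could flag inflated survival, and the quality section names missing records as part of completeness. The full protocol may hold a sampling procedure. Most of this stands and limits the size of the point. It does not remove the conflict, since a rule held elsewhere would leave the abstract and the inclusion criteria opposed. Nor can the population comparison separate selection within a centre from referral to expert centres.

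A reader might infer more than the article supports:

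- **That 1700 is a ceiling.** It appears to rest on a minimum of 100 per centre, so full entry could exceed it.
- **That entering half gives 850 a year.** This also halves the Dutch count, which covers the whole country.
- **That entering half leaves 40 middle ear cases in 4 years.** The figure of 80 is offered as an example and is not derived from 1700. The Introduction's case numbers (200 of 2,500 + 2,500 + 8,000 + 200 = 13,200) would give 1700 × 4 × 200 / 13,200, about 103.
- **That centres could not be compared on quality.** No such comparison is planned.
- **That no model could correct the selection.** Selection that depends on measured covariates can be adjusted for, and silence about a log does not show that none exists.
- **That early deaths before 2021 are lost through the limit.** The requirement of active follow-up already excludes them. That is a separate matter.

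**Conclusion.** The point holds as a contradiction in the text together with an unstated selection rule. The abstract claims complete entry; the inclusion criteria allow partial entry and do not say which patients are taken. For patients managed before recruitment opened, the choice can be made with the 1-year outcome known, so absolute percentages may be biased. How far is unknown. The figures of 85.7% and 88.9% against a true 80% rest on assumed entry rates and describe only patients chosen in that way. The expected 1700 a year is arithmetically sound but presupposes full entry of the counted caseloads.

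**What to change.** Keep the resource limit and reconcile the two statements as follows.

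1. **Entry rule.** A centre that cannot enter all eligible patients enters either consecutive patients by date of first attendance or a random sample from its list of eligible patients. The choice is made without reference to outcome.
2. **Counts.** Each centre reports every year the number of eligible and of entered patients by cancer site. Reports give the fraction entered, and analyses weight by its inverse where random sampling was used.
3. **Abstract.** Withdraw or qualify the statement that no sample is selected.
4. **Limitations.** Add selection within centres, and note that the comparison with population-based data cannot separate it from referral to expert centres.
5. **Sample size.** State that 1700 a year assumes full entry of the counted caseloads, show the sum, and say that the yield will be lower to the extent that centres enter fewer.

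The cost is a change of wording, one yearly count per centre from hospital lists, and less freedom in choosing records. No extra patients or visits are needed. Eligible patients who were never listed are hard to reconstruct later, so the change is best made while recruitment is under way.
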